### Data Collection

#### Overview (Figure 1)

We will assess specific core and recommended clinical outcomes for weight management interventions(47). There will be two in-person study visits and one remote study visit. Participants will be remunerated $240 for their time, with payments disbursed in two installments. The first payment will be disbursed immediately after completion of Visit 1 and the second after Visit 3. After obtaining written consent during the first visit, data collection will begin with measurements of blood pressure, skin temperature, and oxygen saturation (pulse oximetry). Pain and fatigue at rest will be evaluated, followed by anthropometric measurements and a brief screening for large-fiber peripheral neuropathy. Participants will then undergo clinical assessments of bilateral knee and lumbar spine range of motion using goniometry and gravity-dependent inclinometry, and quadriceps strength will be measured with hand-held dynamometry. Next, a standardized quantitative sensory testing battery will be administered to evaluate pain sensitivity using pressure pain threshold (PPT), mechanical temporal summation (TS), cold tolerance via the cold pressor test, and descending pain inhibition through conditioned pain modulation (CPM). Following this, participants will complete a series of questionnaires in either English or Spanish prior to the administration of performance-based assessments of physical function. Finally, participants will perform a standardized series of evocative movement tasks, which will be recorded using camera-based motion capture (stereophotogrammetry). At the first follow-up visit (3 months), participants will complete pain questionnaires and health surveys either via the REDCap secure online platform or by telephone with a research staff member. During the second follow-up visit at 6 months (Visit 3), the tests and measures completed during the first study visit will be repeated. The anticipated time to complete Visits 1 and 3 will be 2.5 – 3.0 hours, and 0.5 – 1.0 hours for Visit 2. Table 2 provides a detailed summary of the data collection protocol and study timeline.

### Data Management and Security

All demographic, vital signs, anthropometric, pain, physical function, and health-related data will be entered into the Research Electronic Data Capture tool (REDCap). The Research Electronic Data Capture (REDCap) tool, hosted by NYU CTSI, will be used for study data collection and management(48, 49). REDCap is a validated web-based software platform that supports data entry, auditing, and tools for data export and integration. Data will also be manually entered on hard copies of data collection documents to ensure data fidelity. Data standards will be employed when using the NIH Common Data Elements Repository (CDE), the Phenotypes and Exposures (PhenX) Toolkit (https://www.phenxtoolkit.org/), and the Patient-Reported Outcomes Measurement Information System (PROMIS)(50). A bilingual study team member fluent in English and Spanish will administer all surveys and questionnaires. Data will be collected at baseline (Visit 1), 3 months after bariatric surgery (Visit 2), and 6 months after bariatric surgery (Visit 3), the primary study endpoint. Upon request, participants can complete hard copies of surveys or complete them in person at Visit 1 and 6 months post-surgery (Visit 3). For Visit 2, participants can complete digital surveys using the secure REDCap tool or review surveys with bilingual research personnel via telephone or a secure HIPAA-compliant web conferencing platform. All study data will be managed and shared in accordance with the principles outlined in the HHS regulatory guidelines for the protection of human subjects (45 CFR 46). Data will be de-identified using the participants’ assigned study identification number. Study data will be stored for 3 years after the last participant completes the last study visit or for 5 years after the final manuscript is accepted for publication. Study monitoring will occur in 6-month intervals to assess recruitment progress and for interim analyses, primarily descriptive statistics and data quality assessment.

### Anthropometric Measurement and Health Status

Anthropometric and health conditions will be collected at all time points, guided by the bariatric surgery Core Registry Set (CRS)(51) and the Standardised Reporting of Lifestyle Weight Management Interventions to Aid Evaluation (STAR-LITE)(47).

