## Abstract

Chronic widespread pain (CWP) is highly prevalent among minoritized adults with clinical obesity, and symptom management is challenging. Weight loss via bariatric surgery is often recommended to improve musculoskeletal pain. However, there is significant variation in pain trajectories following bariatric surgery, and the impact of weight loss on movement-evoked pain is largely unknown. The current study aims to systematically characterize and quantify longitudinal changes in pain at rest and movement-evoked pain up to 6 months post-surgery, and to determine whether pain modulatory mechanisms, joint motion, and mechanical loading biosignatures mediate the relationship between weight loss and pain change. This study protocol details the research methodologies and procedures for a prospective observational cohort study of 60 individuals undergoing bariatric surgery for weight loss. Participants will complete questionnaires, anthropometric measurements, clinical and experimental pain testing, functional testing, and a standardized movement testing battery to assess joint motion and mechanical loading using camera-based motion capture before and at 3 and 6 months post-bariatric surgery. Generalized linear mixed models to assess the significance of changes in PAR, MEP, and all patient-reported outcome measures. Reduced models will treat the main effect of time as a fixed factor, and intra-individual repeated measures as random effects. Ethics and dissemination: This study protocol has been registered as an observational study with ClinicalTrials.gov (NCT0675386), version #1, in the United States and has been approved by the NYU Langone Health Institutional Review Board (IRB#: i21–01652) and the New York City Health + Hospitals/Bellevue Research Office (Bellevue Study ID #: STUDY00003739). Study results will be published in peer-reviewed journals and presented at national and international conferences and community events.

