### Sample Size Determination

The sample size needed to achieve the study's primary aim was determined using extant clinical data from a longitudinal observational cohort study of surgical weight loss(43) (NYU IRB# 16–01995). The primary objective of the study is to characterize and quantify changes in pain at rest (PAR, primary outcome) and MEP (secondary outcome). Power analyses were conducted based on the anticipated within-person mean change in pain at rest from baseline to 6 months post-surgery (primary outcome). Additionally, the clinical assumptions supporting our sample size determinations were the minimum clinically important difference (MCID) for the Brief Pain Inventory (BPI) average pain (2.1 points) and BPI Severity (2.2 points) scores in adults with fibromyalgia (44). The sample size was calculated to detect a Cohen’s d of 0.50 for BPI Severity scores at 3 months, based on a secondary analysis of the parent study cohort, which revealed a sharp reduction in pain intensity ratings in a stratified cohort of NHB and/or Hispanic/Latino/a/X/e adults(22). We considered a 1-point reduction in pain interference at 6 months to be conservative, as proposed in the Initiative on Methods, Measurement, and Pain Assessment in Clinical Trials (45). The sample size calculation assumed a Type I error rate of 2.5% to account for multiple comparisons and 90% power. We estimated a sample size of 50 using a two-sided paired t-test. Thus, we will recruit at least 60 participants to account for a 20% attrition rate, although attrition in the target study population may be higher(46).

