#### Anthropometric measurement

Standardized BMI and waist circumference measurements will be collected using the PhenX BMI Toolkit (https://www.phenxtoolkit.org/ PhenX Toolkit. (2025 September 06). Waist Circumference - Waist Circumference NCFS. https://www.phenxtoolkit.org/protocols/view/21602). Body weight (kg) will be measured in light clothing, without shoes, using a Stow-A-Weigh digital bariatric hospital scale (Scale-Tronix, Welch Allyn, Skaneateles, NY, USA). Height (cm) will be measured using a stadiometer (SECA 213, Seca GmBH & Co. KG, Hamburg, Germany). BMI will be calculated using anthropometric measurements (kg/m^2^) and categorized according to the World Health Organization: Class I=30–34.99 kg/m^2^, Class II=35–39.99 kg/m^2^, and Class III=40 kg/m^2^ or higher. Waist circumference measurement is a proxy for central adiposity and is associated with an elevated risk of Type 1 (52) and Type 2 diabetes, dyslipidemia, and cardiovascular disease (53). It will be measured at the midpoint between the iliac crest and the lowest rib (between the 10th and 12^th^ ribs)(54). The umbilicus will be used as an additional anatomical reference point to improve measurement accuracy. The horizontal distance between the left and right anterior superior iliac spines (inter-ASIS distance) will be measured using a tape measure(55). The inter-ASIS distance will be used to assist in biomechanical modeling of the pelvis and lower-extremity segments' position and pose during motion analysis (56). The percentage of total weight loss (%TWL) will be the weight loss outcome variable. The %TWL is the ratio of weight loss after surgery to presurgical weight, calculated as (baseline weight – current weight) / (baseline weight) × 100 (57). The percentage of TWL will be calculated at 6 months after bariatric surgery.

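### The protocol contradicts itself on what is measured at 3 months, and mediators and weight loss defined only over 0–6 months cannot show which of weight loss, mechanism change and pain change came first

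*Protocol article*

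**What the plan says.** All references are to the protocol article.

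- **Measured at every time point.** Anthropometric Measurement and Health Status: "Anthropometric and health conditions will be collected at all time points". The Abstract lists questionnaires, anthropometry, experimental pain tests, functional tests and motion capture, and dates the whole list "before and at 3 and 6 months post-bariatric surgery".
- **Remote 3-month visit.** Data Collection, Overview: "There will be two in-person study visits and one remote study visit". At 3 months, "participants will complete pain questionnaires and health surveys either via the REDCap secure online platform or by telephone". At 6 months, "the tests and measures completed during the first study visit will be repeated". Data Management and Security and Participant Protections also describe the 3-month contact as online, by telephone or by web conference. Physical Function places its performance tests at baseline and 6 months.
- **Weight.** Anthropometric measurement has weight taken on a bariatric hospital scale and adds: "The percentage of TWL will be calculated at 6 months after bariatric surgery". Planned Statistical Analyses reports anthropometric data at baseline and 6 months.
- **Early pain change.** Sample Size Determination bases its 3-month effect size on an earlier cohort analysis "which revealed a sharp reduction in pain intensity ratings". Primary and Secondary Aims cites the group's finding that the slope of pain at rest differs before and after 3 months.
- **Use of the data.** Study Objectives sets an exploratory aim, with hypothesis 3, that mechanism changes mediate the link between weight loss and pain reduction. The Discussion expects the data to test whether reduced joint loading is the main mechanism of pain resolution.

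**The concern.** There are two linked problems. First, the article gives incompatible schedules. Weight on a hospital scale, algometry and force-plate recordings cannot be collected by survey or telephone, so the Abstract and the anthropometry section do not fit the 3-month visit described in the Data Collection overview.

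Second, a mediation claim needs an order: weight loss, then mechanism change, then pain change. On the visit-level schedule, the mediators tested in person and %TWL have one post-surgery reading, at 6 months, while pain is read at 3 and 6 months. If pain falls early, part of the outcome change is complete before any in-person mediator is read again. A positive result could then be taken as evidence of mechanism when the data fit the opposite direction equally well, for example less pain leading to changed movement.

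**Working it through.** **1. Schedule side by side**

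| Measure | Abstract | Anthropometry sections | Data Collection overview and Physical Function |
|---|---|---|---|
| Body weight | 0, 3, 6 months | all time points; hospital scale | in-person visits at 0 and 6 months; 3-month visit by survey |
| %TWL | – | 6 months | – |
| Sensory tests, motion capture, function tests | 0, 3, 6 months | – | 0 and 6 months |
| Pain questionnaires | 0, 3, 6 months | – | 0, 3, 6 months |

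The row for in-person mechanism tests conflicts only with the Abstract. The weight row conflicts within the body text.

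**2. What order the visit-level schedule can show**

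Mediator change is known over 0–6 months only. Three pain changes could serve as the outcome:

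- 0–3 months: complete before the mediator's second reading.
- 3–6 months: lies inside the interval over which the mediator change is measured.
- 0–6 months: the same interval as the mediator.

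None places mediator change before pain change. The same holds for %TWL as defined.

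**3. Equivalence of the two directions**

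Let X = %TWL, M = mediator change and P = pain change, all over 0–6 months. The planned order factors the joint distribution as f(M|X)·f(P|X,M), and the reverse order as f(P|X)·f(M|X,P). Both equal f(M,P|X), so linear normal models fit identically. One simulated data set of 48 gave a log-likelihood (up to a constant) of 7.9325 for each.

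**4. Illustration of size**

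The plan gives no figure for mediation, so there is none to reproduce. Inputs:

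- Sample sizes: 60 recruited (Sample Size Determination), with attrition of 20–40% at 6 months (Discussion). 60 × 0.8 = 48 and 60 × 0.6 = 36.
- Path size b: not in the documents, so assumed.
- Truth set to the reverse order: P = bX + √(1−b²)·e₁ and M = bP + √(1−b²)·e₂. The X–M correlation is then b × b, for example 0.5 × 0.5 = 0.25.
- Test of the planned order: slope of M on X and slope of P on M given X, both p < 0.05; 3,000 runs per setting.

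| n | b | Planned order declared when the reverse is true |
|---|---|---|
| 36 | 0.5 | 24% |
| 48 | 0.5 | 37% |
| 60 | 0.5 | 46% |
| 48 | 0.3 | 5% |
| 48 | 0.5 (separate run) | 35% |
| 48 | 0.7 | 95% |

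For comparison, with the planned order true and b = 0.5, it was declared in 68%, 86% and 94% of runs at n = 36, 48 and 60.

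**The case against.** A fair defence has several parts.

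- **Weight at 3 months is not declared missing.** A reader might infer from the remote visit that no weight is taken then. The documents do not support that: the anthropometry section says the opposite, and a remote visit rules out the study scale but not a record-derived or self-reported weight. The body of Table 2, to which the overview refers for the timeline, is not visible and may settle it. This stands, so for weight the defect is an unresolved contradiction.
- **Some mechanism data may exist at 3 months.** The Central Sensitization Inventory could be among the questionnaires sent. This stands; the point is limited to mediators tested in person.
- **The early fall has no stated share.** A reader might infer that most of the 6-month pain change is over by 3 months. The protocol reports a sharp reduction and a slope difference but no fraction, so only an early fall can be claimed.
- **Some order is known.** Surgery precedes every follow-up measure. This stands; the order that is missing lies among weight loss, mechanism and pain after surgery.
- **The remote visit is a reasonable trade-off.** In-person visits last 2.5–3.0 hours, and work schedules, childcare and commuting are named barriers to retention. This is a good reason not to demand a third laboratory visit. It does not reconcile the text or supply the missing order.
- **The aim is exploratory,** and the Exploratory Aim section itself speaks of association between %TWL and pain. This limits the consequence, but hypothesis 3 and the Discussion still use mechanistic language.

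**Conclusion.** The point holds in limited form. The Abstract and the anthropometry section conflict with the visit descriptions on what is collected at 3 months, and no section says how weight would be obtained then. As written, the in-person mediators and %TWL yield only baseline-to-6-month changes, so the exploratory mediation analysis cannot identify the order of weight loss, mechanism change and pain change after surgery.

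The non-identifiability follows from the schedule and does not depend on any assumed effect size. The simulated rates do: 5% to 95% at n = 48 is a range over assumed paths and is not a forecast for this study. The analysis of change in pain at rest and in movement-evoked pain to 6 months is unaffected. The correction should be made, but it does not threaten the study's main results.

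**What to change.** 1. **Reconcile the schedule.** State in the Abstract that the in-person mechanism and function tests are done at baseline and 6 months only. State in Anthropometric Measurement and Health Status how the 3-month weight is obtained, in line with the Data Collection overview, the %TWL definition and Table 2. Cost: wording.
2. **Obtain a dated 3-month weight from the electronic record.** Health status already uses that record for surgery type, comorbidities and medications. Define %TWL at 3 and 6 months, relate 0–3 month %TWL to 0–3 month change in questionnaire pain, and use 3-month %TWL as the prior exposure for 3–6 month pain change. Only the second comparison puts exposure before outcome; the first is still concurrent. Neither helps movement-evoked pain, which is rated during in-person tasks. Cost: one abstracted field and its date. Clinic weights are less standardised than the study scale, and some will be missing.
3. **Limit the mediation claim.** A 3-month weight does not change when the mediators are read. Report the mediation result as concurrent association without causal order, and soften hypothesis 3 and the joint-loading statement in the Discussion to match. Cost: wording. The alternative, a further in-person mediator assessment at 3 months, would burden participants and is not needed if the claim is limited.

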#### Anthropometric measurement

Standardized BMI and waist circumference measurements will be collected using the PhenX BMI Toolkit (https://www.phenxtoolkit.org/ PhenX Toolkit. (2025 September 06). Waist Circumference - Waist Circumference NCFS. https://www.phenxtoolkit.org/protocols/view/21602). Body weight (kg) will be measured in light clothing, without shoes, using a Stow-A-Weigh digital bariatric hospital scale (Scale-Tronix, Welch Allyn, Skaneateles, NY, USA). Height (cm) will be measured using a stadiometer (SECA 213, Seca GmBH & Co. KG, Hamburg, Germany). BMI will be calculated using anthropometric measurements (kg/m^2^) and categorized according to the World Health Organization: Class I=30–34.99 kg/m^2^, Class II=35–39.99 kg/m^2^, and Class III=40 kg/m^2^ or higher. Waist circumference measurement is a proxy for central adiposity and is associated with an elevated risk of Type 1 (52) and Type 2 diabetes, dyslipidemia, and cardiovascular disease (53). It will be measured at the midpoint between the iliac crest and the lowest rib (between the 10th and 12^th^ ribs)(54). The umbilicus will be used as an additional anatomical reference point to improve measurement accuracy. The horizontal distance between the left and right anterior superior iliac spines (inter-ASIS distance) will be measured using a tape measure(55). The inter-ASIS distance will be used to assist in biomechanical modeling of the pelvis and lower-extremity segments' position and pose during motion analysis (56). The percentage of total weight loss (%TWL) will be the weight loss outcome variable. The %TWL is the ratio of weight loss after surgery to presurgical weight, calculated as (baseline weight – current weight) / (baseline weight) × 100 (57). The percentage of TWL will be calculated at 6 months after bariatric surgery.

#### Sensory Testing

Participants will undergo sensation testing at select sites on the bilateral lower extremities while seated in a chair at standard height with arm support. Light-touch sensation and allodynia will be assessed by applying a cotton ball to the L4-S1 dermatomal distribution over the lower leg, ankle, and foot. Mechanical cutaneous sensation will be assessed using a 5.07 g Semmes-Weinstein monofilament on the foot at the following sites: dorsal surface, between the 2^nd^ and 3^rd^ metatarsals, and the plantar surface of the 1^st^, 3^rd^, and 5^th^ metatarsal heads. The order of application of the cotton ball and monofilament across anatomical sites will be randomized.

#### Health status

Surgical intervention type (Roux–en–Y, sleeve gastrectomy, or Lap-Band), medical comorbidities (e.g., diabetes, cardiovascular health), and current medications for pain and other health conditions will be obtained from participants’ electronic medical records.

### Pain Measurement and Assessment

#### Pain Intensity at Rest (PAR)

Pain intensity at rest (PAR) will be evaluated using the Numeric Pain Rating Scale (NPRS) and the Brief Pain Inventory – Short Form (BPI-SF).

#### Numeric Pain Rating Scale (NPRS)

The NPRS is a single-item pain intensity scale ranging from 0 (no pain) to 10 (worst pain imaginable). The NPRS has been validated in Spanish-speaking populations(58).

#### Brief Pain Inventory – Short Form (BPI – SF)

The BPI-SF is a 9-item self-assessment that measures pain intensity, interference with physical functioning, and pain location(59). The BPI-SF Pain Severity and Pain Interference subscales feature anchors from 0 (“no pain”) to 10 (“Pain As Bad As You Can Imagine”), and the subscale score is the mean of the four items. The BPI-SF Pain Interference subscale is the mean of 7 items. The BPI-SF has been validated in Spanish (60) and in adults undergoing bariatric surgery (61, 62). The BPI-SF assesses pain domains recommended by the Initiative on Methods, Measurement, and Pain Assessment in Clinical Trials (IMMPACT)(45, 63). Pain at rest will be measured before vital signs and anthropometric measurements are taken.

#### Movement-Evoked Pain (MEP)

MEP intensity will be a secondary outcome of this study and will be calculated as a composite score of pain intensity ratings across a battery of functional movement tasks (64). MEP will be measured during objective measures of physical function (5TSTS, 6MWT) and during a standardized battery of 4 evocative movement tasks: seated knee extensions, walking, picking up a 5 lb. (2.27 kg) weight, and ascending and descending a 6-inch step. More detailed descriptions of each movement task are provided below. During the 6MWT, participants will rate their pain intensity using the NPRS (0 = no pain, 10 = worst pain imaginable) before the test. Participants will rate their pain at the 5-minute mark of the test and again immediately after the 6MWT. During the 5TSTS, participants will rate their pain immediately and 60 seconds after the last repetition.

Pain intensity ratings and location will be obtained immediately following and 30 seconds after evocative pain tasks using the NPRS for the standardized movement testing battery. The MEP composite score will be calculated as the average pain intensity rating across all movement tasks, divided by the number of movement tasks. MEP aggregate scores will be calculated separately for objective functional measurements and for the standardized evocative task movement testing battery. Higher scores indicate greater MEP.

$${MEP\;intensity}_{\text{physical}\;\text{function}\;}=\left[\left(MEP_{5TSTS}\right.\right.\;+\;MEP_{6MWT})/2]$$

$${\text{MEP}\;\text{intensity}}_{\text{movement}\;\text{battery}}=\left[\left({\text{MEP}}_{\text{knee}\;\text{ext}}\right.\right.+{\text{MEP}}_{\text{walk}}+{\text{MEP}}_{\text{object}\;\text{pickup}}+\text{MEP}\left.\left.{\text{step}\;}_{\text{down}}\right)/4\right]$$

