#### Conditioned Pain Modulation (CPM)

We will perform conditioned pain modulation (CPM) to assess the function of descending inhibitory pathways responsible for endogenous analgesia (80). The total duration of CPM testing will be 2 minutes. We will use the parallel CPM paradigm, which has been shown to elicit a more robust inhibitory response in women with fibromyalgia (81). The test stimulus will be mechanical pressure applied at the upper trapezius using a pressure algometer contralateral to the hand submerged in cold water. The conditioning stimulus will be cold-water immersion of the non-dominant hand up to the wrist in an 8 °- 12 °C water bath. PPT will be measured immediately before (PPT1) and 60 seconds after (PPT2) cold water immersion. Pain intensity will be assessed at 20, 60, and 120 seconds after cold water immersion. The average of 3 PPT measurements at the upper trapezius will be included in the analyses. The percent change in PPT2-to-PPT1 values (PPT2/PPT1) × 100 and the absolute effect (PPT2 – PPT1) will be calculated. Lower values indicate impaired function of descending inhibitory pathways. This protocol has been used in women with fibromyalgia and higher BMI (82, 83). Details are outlined in **Supplementary Figure 3**.

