The movement testing battery will include bilateral seated knee extension, overground walking, picking up a weight from a step (object pick-up task), and a bilateral step-down task (Figure 3). Participants will be given scripted instructions in either English or Spanish on how to perform each movement task and will complete one practice trial before recording. Participants will perform knee flexion and extension while sitting on a stool for the seated knee extension task. The stool will be adjusted to the participants’ height to maintain 90 degrees at knee flexion with the thighs parallel to the floor. Two trials will consist of 5 repetitions per leg, and the average of each trial will be used in all statistical analyses. For the walking task, participants will perform 5 trials over a 13 ft (396.2 cm) walkway at their self-selected gait speed. Gait speed will be included as a covariate in statistical analyses because it is associated with weight or BMI(111). The average of 3 trials will be used for statistical analyses. For the object pick-up task, participants will pick up a 5-lb (2.27 kg) weight from a 6-inch (15.2 cm) step and return it to its original position. There will be 3 trials of this task, and the average will be included in statistical analyses. For the step-down task, participants will be asked to ascend and descend a 6-inch step with the same lower extremity. There will be 2 trials for each lower extremity, and the average across trials will be included in the statistical analyses. The primary kinematic variables to be analyzed are peak knee flexion and extension, and peak trunk flexion and extension, across all movement tasks. The primary kinetic variables to be analyzed are peak knee and trunk extension moments (N · m/kg). We will include additional kinematic and kinetic variables in our exploratory analyses. Participants will rate their PAR before the practice trial. Upon completion of the last trial of the movement task, participants will be asked to rate their pain immediately and 1 minute after task completion.

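### Three measurement rules are inconsistent as written: the MEP composite sentence against its own equations, the delayed rating time for the movement battery, and the CPM ratio labelled as a percent change

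*Protocol article*

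**What the plan says.** **MEP composite (Movement-Evoked Pain section).** The prose rule is: "The MEP composite score will be calculated as the average pain intensity rating across all movement tasks, divided by the number of movement tasks". The section then keeps two scores apart: "MEP aggregate scores will be calculated separately for objective functional measurements and for the standardized evocative task movement testing battery". It prints an equation for each. The physical-function score is the 5TSTS and 6MWT ratings added and divided by 2. The movement-battery score is the four task ratings added and divided by 4.

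**Timing of the battery ratings.** The same section says of the standardized battery: "Pain intensity ratings and location will be obtained immediately following and 30 seconds after evocative pain tasks using the NPRS". The Motion Analysis section, describing the same four tasks, says that "participants will be asked to rate their pain immediately and 1 minute after task completion".

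**CPM (Conditioned Pain Modulation section).** The scoring rule is: "The percent change in PPT2-to-PPT1 values (PPT2/PPT1) × 100 and the absolute effect (PPT2 – PPT1) will be calculated". The direction rule follows: "Lower values indicate impaired function of descending inhibitory pathways".

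Study Objectives makes MEP the secondary outcome. It also aims to quantify change in pain modulation at 6 months, and places mediation in an exploratory, tertiary aim.

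**The concern.** These are operative rules for collecting and scoring data, and each conflicts with another rule or with its own label.

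- **MEP.** The sentence and the equations give scores that differ by a factor of 4 (battery) or 2 (physical function). The first working hypothesis expects clinically significant reductions in MEP. A score compressed to a quarter or a half of its range could not be read on the 0–10 scale used for pain at rest, and the two composites would no longer share a scale.
- **Timing.** Pain after a movement task may fall with time, so ratings at 30 seconds and at 1 minute need not measure the same quantity. The analysis compares baseline with 6 months within each person. If the delay differed between visits or raters, that difference would mix with true change in the delayed rating. Study Setting says that recruitment began on August 1, 2023 and that data collection is ongoing, so the question already bears on collected data.
- **CPM.** A reader who trusts the label takes 0 as no modulation. On the printed formula that point is 100, so a value such as 90 looks like a large positive effect when it means the threshold fell.

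**Working it through.** The plan states no numerical result for these scores, so there is no figure to reproduce. The check compares the rules. Pain ratings and thresholds below are assumed for illustration.

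**1. MEP: sentence against equations**

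Inputs: k = 4 battery tasks and k = 2 physical-function tasks (MEP section); ratings 0–10 (NPRS section).

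- Equation: score = (sum of k ratings)/k. Maximum = 10 for either score.
- Sentence read literally: score = [(sum of k ratings)/k]/k. Maximum = 10/4 = 2.5 for the battery and 10/2 = 5 for physical function.

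| Assumed ratings | Equation | Literal sentence |
|---|---|---|
| Battery, baseline 6, 5, 7, 6 | 24/4 = 6.0 | 6.0/4 = 1.5 |
| Battery, 6 months 4, 3, 5, 4 | 16/4 = 4.0 | 4.0/4 = 1.0 |
| Battery, change | 2.0 | 0.5 |
| Physical function 6, 6 | 12/2 = 6.0 | 6.0/2 = 3.0 |

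A 2-point change on the physical-function score would read 2/2 = 1.0.

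Effect on testing: a paired t statistic is the mean change over its standard error. Dividing every score by the same k divides both by k, so t and p stay the same. Simulated ratings for 50 people confirmed this: mean change was 1.04 by the equation and 0.26 by the sentence, with t = 10.11 both times. Only the magnitude changes.

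**2. Rating times, side by side**

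| Measure | MEP section | Motion Analysis section |
|---|---|---|
| Battery, first rating | immediately after | immediately after |
| Battery, second rating | 30 seconds after | 1 minute after |

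The immediate rating agrees. The 60-second rating in the MEP section belongs to the 5TSTS, not to the battery, so it does not explain the difference. The 6MWT times in the MEP and Physical Function sections are compatible. The conflict is therefore confined to the delayed battery rating. The battery equation has one term per task while each task yields two post-task ratings, and the article does not say whether the delayed one contributes.

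**3. CPM: ratio against percent change**

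- Printed: R = (PPT2/PPT1) × 100.
- Percent change: C = (PPT2 − PPT1)/PPT1 × 100 = R − 100.

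| Assumed PPT1, PPT2 (kPa) | R | C |
|---|---|---|
| 200, 200 | 100 | 0 |
| 200, 220 | 110 | +10 |
| 200, 180 | 90 | −10 |

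The gap is 100 for every person. The between-visit change is therefore the same on both: (R at 6 months − 100) − (R at baseline − 100) = R at 6 months − R at baseline. In simulated data for 50 people the SD was 18.21 on both versions, and a regression of an outcome on each gave the same slope (0.00651) and p-value (0.349). Only the intercept moved.

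**The case against.** The strongest reply concerns consequence.

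- **MEP.** The equations stand directly below the sentence and define both scores as ordinary means on 0–10. The sentence is most naturally a clumsy description of an average. This stands. A reader might infer that the secondary outcome will be mis-scaled, but that requires the sentence to override the equations, and nothing in the article suggests that it does.
- **CPM.** The formula shifts the measure by a constant and does not rescale it. The absolute effect, PPT2 − PPT1, is also planned and has its null at 0, and the direction rule holds for both quantities. This stands too. A reader might expect a test of the mean against 0 to reject with no modulation present, but the statistical sections describe changes over time, correlations, mixed models and group comparisons, and state no such test. Nor do the documents support calling CPM a key mediator: it is one of several pain-modulation measures, considered beside joint motion and loading in an exploratory aim.
- **Timing.** The article does not say that the delayed rating enters the composite, so the conflict is not shown to reach the secondary outcome. That is correct and limits the claim. It does not remove a contradiction about when a rating is taken.
- **Detail left elsewhere.** Which of several ratings feeds each task term, and whether one composite leads, may be settled in a full protocol or analysis plan not shown here. Leaving those open is no fault of an article, and this point does not ask for the composites to be ranked. Two sections giving different times for one measurement is a different matter.

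**Conclusion.** The point holds as three inconsistencies in wording and procedure, not as evidence that results will be wrong.

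1. The MEP sentence contradicts its equations by a factor of 4 or 2. If it were followed, magnitudes and their clinical interpretation would be wrong while p-values would not change. If the equations are followed, there is no harm.
2. The delayed battery rating has two incompatible times. This is the weightiest of the three, because no equation resolves it and inconsistent timing cannot be repaired after collection. Its numerical effect cannot be sized from the article, which does not say how pain decays between 30 seconds and 1 minute, which delay has been used, or whether the rating enters the composite.
3. The CPM quantity is mislabelled by a constant 100. Between-visit changes, slopes and mediation paths are unaffected; reported levels and the no-effect point would be misread.

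The scaling conclusions are algebraic and do not depend on the assumed ratings or thresholds.

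**What to change.** - **MEP sentence:** reword it as the sum of the task ratings divided by the number of tasks, to match both equations.
- **Battery timing:** reconcile the MEP and Motion Analysis sections to one delay. Check the data collection forms and scripts for the delay actually used since recruitment began, and confirm that baseline and 6-month ratings are comparable. If both delays have been used, record which applies to each visit. State whether the delayed rating enters the composite.
- **CPM formula:** either define percent change as (PPT2 − PPT1)/PPT1 × 100, or keep the printed formula and call it PPT2 as a percentage of PPT1, noting that 100 means no change.

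Cost: short edits in three sections, a check that the scoring code follows the equations, and a look through site records for the delay. No change to sample size, visits or planned models.
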